## Abstract

**Background:**

Many teenagers are insufficiently active despite the health benefits of physical activity (PA). There is strong evidence to show that inactivity and low fitness levels increase the risk of non-communicable diseases such as coronary heart disease (CHD), type 2 diabetes and breast and colon cancers (Lee et al. Lancet 380:219–29, 2012). A major barrier facing adolescents is accessibility (e.g. cost and lack of local facilities). The ACTIVE project aims to tackle this barrier through a multi-faceted intervention, giving teenagers vouchers to spend on activities of their choice and empowering young people to improve their fitness and PA levels.

**Design:**

ACTIVE is a mixed methods randomised control trial in 7 secondary schools in Swansea, South Wales. Quantitative and qualitative measures including PA (cooper run test (CRT), accelerometery over 7 days), cardiovascular (CV) measures (blood pressure, pulse wave analysis) and focus groups will be undertaken at 4 separate time points (baseline, 6 months,12 months and follow-up at 18 months). Intervention schools will receive a multi-component intervention involving 12 months of £20 vouchers to spend on physical activities of their choice, a peer mentor scheme and opportunities to attend advocacy meetings. Control schools are encouraged to continue usual practice. The primary aim is to examine the effect of the intervention in improving cardiovascular fitness.

**Discussion:**

This paper describes the protocol for the ACTIVE randomised control trial, which aims to increase fitness, physical activity and socialisation of teenagers in Swansea, UK via a voucher scheme combined with peer mentoring. Results can contribute to the evidence base on teenage physical activity and, if effective, the intervention has the potential to inform future physical activity interventions and policy.

**Trial registration:**

ISRCTN75594310 (Assigned 06/03/2017).

## Background

Being active in adolescence is associated with many health benefits [1–6] and physical activity (PA) levels established during this time are likely to be taken into adulthood [2]. However, reports show that many adolescents are not sufficiently active to achieve these benefits [2, 7]. Government recommendations for PA suggest adolescents should be engaging in at least 60 min of moderate to vigorous physical activity (MVPA) every day [8]. A large proportion of young people do not meet this recommendation in Wales [9], with recent evidence showing that only 11% of girls and 20% of boys are sufficiently active [10]. This is concerning, as there is strong evidence to show the increased risk of non-communicable disease such as CHD, reduced well-being and shortened life expectancy resulting from inactivity and low aerobic fitness levels [11, 12].

Given that 7 million people in the United Kingdom are fighting CV diseases, [13] with physical inactivity a major risk factor, the development of effective interventions to promote activity in adolescence is of urgent public health concern [14]. It is reported that one of the main barriers to PA for teenagers is accessibility (e.g. cost and lack of local facilities) [8, 15], particularly for teenagers from disadvantaged backgrounds [4]. There is also a population trend towards spending more time inside, where technology can increase screen time and sedentary behaviours [3, 6].

The Active Children through Individual Vouchers – Evaluation Project (ACTIVE), funded by the British Heart Foundation (BHF) [16], aims to tackle these barriers and increase PA by giving teenagers vouchers to spend on activities of their choice. The project encourages teenagers to access existing provisions or generate their own in order to tackle accessibility issues and create the opportunity to participate in desired activities [15]. Evidence has shown that empowering teenagers to make their own choices over which activity they engage in, the location where they engage, and the people they participate with, can improve activity levels [17]. ACTIVE will also encourage teenagers to express the importance of choice and empowerment in advocacy meetings with stakeholders. As a result, the project aims to enhance socialisation and peer support, in order to facilitate PA uptake. This has been positively associated with teenage activity levels [18].

A voucher based intervention to increase PA in the UK has been previously tested amongst adults [19, 20], however, it remains uncertain whether a similar approach could work with teenagers. Financial incentives have been previously tested within a variety of populations [21–24] and have been effective in increasing physical activity levels. However, these focus on financial rewards rather than activity enabling vouchers. The ACTIVE Project aims to investigate whether a multi-component voucher based scheme can positively influence teenagers to become more physically active and improve their cardiovascular fitness.

## Feasibility study

The ACTIVE feasibility study [15] was a mixed method cohort and process evaluation study of one school in a deprived area of Swansea, South Wales. The school was classed as deprived based on: i) the number of pupils eligible for free school meals (FSM) (54% at time of study) [25], ii) the area’s eligibility for community-based initiatives and funding (e.g. Communities First) [15] and iii) the location in one of Wales’ most deprived areas for children [26]. The study measured outcomes at three different time points (baseline, 5 months (during intervention) and 12 months (follow-up)). All Year 9 pupils in the school were given activity vouchers (*n =* 115; 13.3 ± 0.48 years; 51% boys).

The project found increases in MVPA and decreases in sedentary behaviour, suggesting a positive impact from voucher usage [15]. Process evaluation based on the RE-AIM Framework [27] demonstrated that ACTIVE was well received by pupils and teachers and was a feasible approach to increasing PA amongst adolescents from low socio-economic backgrounds.

Adjustments were made to the ACTIVE protocol following outcomes, process evaluation and recommendations from funding partners. These adjustments were made to further improve the project and increase its sustainability, prior to conducting a Randomised Controlled Trial (RCT) in order to assess effectiveness rather than its feasibility.

## Aims

The current study builds upon the feasibility study by examining the effect of a multi-component voucher based intervention on the cardiovascular fitness and MVPA levels of teenagers aged 13–14 years in seven schools in Swansea (4 intervention and 3 control schools). The specific aims of the ACTIVE Project are as follows:

### Primary aims

To examine evidence of the effect of a multi-component intervention in improving cardiovascular fitness based on Cooper Run Test score.

### Secondary aims

2.To examine evidence of the effect of a multi-component intervention in reducing time spent sedentary, as measured by 7-day accelerometry.3.To determine the effectiveness of the ACTIVE intervention to improve the following secondary outcomes:
The amount of teenagers meeting the recommendation of 60 min of MVPA per day.Cardiovascular health (blood pressure and pulse wave analysis (PWA) an indicator of arterial stiffness).Exercise motivation (BREQ-2).The characteristics of teenagers who engage with the scheme, particularly among high risk groups to determine what works for whom, why and in what contexts.
4.To examine evidence of the effect on sustained local investment in implementing recommendations of teenagers in promoting PA and cost-effectiveness.5.To provide evidence of whether ACTIVE can have a sustainable effect on fitness and PA (18-month follow-up)6.To provide evidence that ACTIVE can be implemented by the local council with future rollout to other areas.7.To undertake data linkage of quantitative measures through the Secure Anonymised Information Linkage (SAIL) databank [28] to analyse the effects of physical activity levels on educational attainment and GP visits.

## Design

ACTIVE is a mixed methods randomised controlled trial based in state secondary schools in Swansea, South Wales. Schools will be approached to take part due to their: i) location in one of Wales’ most deprived areas and ii) location in a Communities First catchment area [29, 30]. Randomisation will occur prior to baseline data collection with schools randomised into either the intervention arm or control arm. Due to the nature of the study, participants will be aware of which arm they have been allocated to.

The College of Human and Health Science Ethics Committee at the College of Medicine, Swansea University granted ACTIVE ethical approval on 12/05/2016.

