## Participant recruitment

Following initial school recruitment, participants will be recruited for primary and secondary outcome measures via Year 9 assemblies. During the assemblies, researchers on the project (DC & MJ) will provide information about the project and answer any questions before distributing project information, parental consent and pupil assent forms after the assembly. Once consent and assent has been obtained, participants will be eligible to partake in the study.

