### Peer mentoring scheme, advocacy meetings and pupil-led video production

Prior to baseline measures, pupils from each school will be asked to identify key influencers to be peer mentors (10 from each school). A peer nomination questionnaire was given to all pupils in the year and those who received the most nominations were invited to be peer supporters [31]. These individuals will receive training to be ‘peer supporters’ from the Active Young People team at Swansea Council and a student from the PR and Marketing Taught Masters course at Swansea University. The role of peer supporter is to encourage the uptake and sustainability of physical activity. This approach has been underpinned by ASSIST (A Stop Smoking in Schools Trial); an intervention which involved training Year 8 students to promote the benefits of not smoking amongst their peers. [32].

Peer mentors will be encouraged to produce videos throughout the intervention to explain why activity is important to them, the barriers to being active and any recommendations to improve activity for teenagers. These will help provide an innovative way to display the work of the ACTIVE intervention at advocacy meetings. These videos will be uploaded to YouTube and shown to local stakeholders and providers. Using an ACTIVE profile, videos will be recorded via ‘Snapchat’, a popular image-messaging app. Studies have shown that ‘Snapchat’ is used to facilitate relationships and ‘bonding’ amongst social circles [33, 34] and combined with its use of filters and text will create a novel way of displaying physical activity perceptions of this age group.

Throughout the ACTIVE intervention, advocacy meetings will be held with key stakeholders in order to promote sustainable investment for the provision of physical activities in the local community. These meetings will occur at 6 months and 12 months and involve discussion of needs, barriers to activity and changes that could improve teenager’s access and uptake from the peer mentors’ point of view.

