**INTERVENTION FOCUS GROUP TOPIC GUIDE – PARTICIPANTS – PRE-INTERVENTION.**

*Activity 1 (5–10 min):* What is physical activity? What does it mean to you?

*(Ask pupils to discuss/write down what the term means to them).*

How active should people your age be? (60 min recommended per day).

*Question 1:* How active do you think people in your year are? Do you think you are as active as you can be?

*Activity 2 (5–10 min):* What do you see as the current barriers to physical activity? How do you feel about your current levels?

*(Give post-it notes and ask pupils to list 5–6 barriers to activity. Then rank these barriers in order of most common barriers and discuss the reasoning for this order).*

*Question 2:* Why do you think people your age like/don’t like being active? Is there much to do in your area? If so, how accessible are these activities to your age group?

*Question 3:* Vouchers are currently accepted by *(refer to list of participants).* What other activities or providers would you like to see included before we start?

*Question 4:* Having heard the way the scheme is set up; do you think there will be any problems? What do you think we could do about these problems? Do you think we should do things differently?

*Question 5:* What is the best way of letting everyone in the school know about this scheme? When are the best times for the support worker to be available in the school?

*Question 6:* Do you have anything else to add about the project?

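### Schools are randomised before baseline with the arm known, and consent is not said to come first, so the baseline Cooper run, and possibly who consents, can depend on allocation

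*Protocol article*

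**What the plan says.** The Design section fixes two things: "Randomisation will occur prior to baseline data collection with schools randomised into either the intervention arm or control arm", and "participants will be aware of which arm they have been allocated to".

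On pupil entry, the Participant recruitment section says: "Following initial school recruitment, participants will be recruited for primary and secondary outcome measures via Year 9 assemblies". At these assemblies project researchers "will provide information about the project and answer any questions before distributing project information, parental consent and pupil assent forms after the assembly". The section ends: "Once consent and assent has been obtained, participants will be eligible to partake in the study". It does not place consent before or after randomisation.

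Two other places bear on what pupils may know around baseline. The peer mentoring section says: "Prior to baseline measures, pupils from each school will be asked to identify key influencers to be peer mentors". The pre-intervention focus group guide for intervention schools in Appendix 1 asks: "Having heard the way the scheme is set up; do you think there will be any problems". The control guide has no comparable question.

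The primary outcome is the Cooper Run Test, done in PE lessons at all four time points. The Analysis section lists baseline scores among the variables adjusted for.

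**The concern.** In a trial that randomises schools, randomisation protects the comparison of the pupils analysed only if their entry and their baseline values do not depend on the arm. A timed walk/run distance depends on how hard the pupil tries. If pupils know when they run the baseline test that their school will, or will not, receive the scheme, effort may differ between arms before any intervention is delivered. A covariate already affected by allocation passes part of that difference into the adjusted treatment effect.

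If consent is also sought with the arm known, the consenting groups may differ in fitness or motivation for reasons unrelated to the intervention. With only seven schools (four intervention, three control), sizeable chance imbalance is likely. Baseline adjustment is then one of the main protections, so a weakened baseline matters more here than in a large trial.

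**Working it through.** **1. Order of events**

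| Event | What the article states |
|---|---|
| School recruitment | Before pupil recruitment |
| Randomisation of schools | Before baseline data collection |
| Pupil consent and assent | After school recruitment; order relative to randomisation not stated |
| Peer nomination | Before baseline measures, in each school; arm not specified |
| Knowledge of arm | Participants know it; when they learn it is not stated |
| Baseline Cooper run | After randomisation |

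The text therefore establishes that baseline follows randomisation and that the trial is open to pupils. It leaves open whether consent follows randomisation. It describes no safeguard, such as consent before allocation, masked recruitment, or withholding the allocation until baseline is complete.

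**2. Reference scale**

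The Analysis section assumes improvements of 98 m (intervention) and 22 m (control), so the planned difference is 98 − 22 = 76 m. The concern rests on no other stated figure, and no stated sample size changes because of it.

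**3. How a baseline shift carries through (assumed inputs)**

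With baseline adjustment, the estimated effect is (difference in follow-up means) − β × (difference in baseline means), where β is the slope on baseline. If knowing the arm raises the intervention schools' baseline by s metres relative to control and leaves follow-up unchanged, the bias is −β × s.

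Neither s nor β is in the document. Taking s = 20 to 40 m and β = 0.5 to 0.9:

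- smallest: −0.5 × 20 = −10 m, and 10/76 = 13% of the planned difference;
- middle: −0.7 × 20 = −14 m, and 14/76 = 18%;
- largest: −0.9 × 40 = −36 m, and 36/76 = 47%.

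In this direction the bias works against the intervention. If control pupils were the ones to try harder at baseline, s would be negative and the bias would favour the intervention.

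**4. How selective consent would carry through (assumed inputs)**

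Suppose 80% consent in intervention schools and 60% in control schools, with the extra consenters differing by d = 50 to 150 m. They make up (0.80 − 0.60)/0.80 = 0.25 of the intervention sample, so the raw shift in its mean is 0.25 × d = 12.5 to 37.5 m. If the difference is stable fitness, the baseline measures it and adjustment removes the share β. With β = 0.7 the remainder is 0.3 × 12.5 = 3.75 m to 0.3 × 37.5 = 11.25 m, or about 5% to 15% of 76 m.

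The article's only consent figure is a single 60% scenario, not split by arm. Steps 3 and 4 can have opposite signs, so they should not be added.

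**The case against.** The strongest counter-case is that only the order of randomisation and baseline is actually stated. Much of what a reader might add is inference.

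- **Recruitment after allocation.** A reader might infer that pupils are recruited once their school's arm is known. The article does not say so, and a condensed article need not spell out the order. This stands: the consent part is an open risk, not a stated fact.
- **Vouchers as an inducement.** A reader might infer that £20 a month draws intervention pupils into consenting. The article describes recruitment for outcome measures, and in the feasibility study all Year 9 pupils received vouchers. The closing sentence on eligibility is ambiguous, but nothing makes vouchers conditional on consent. This also stands. Control schools, moreover, receive a mindfulness course for taking part.
- **Peer nomination.** It is described for each school, with no arm specified. If done in every school it does not differ by arm. This stands.
- **The topic guide.** The scheme may have been explained within the focus group session, and those pupils have already consented. The guide shows that arm-specific information exists around baseline, not that pupils held it before consenting or before the run.
- **Effort.** The run takes place in ordinary PE lessons, and nothing in the article shows that effort differs by arm. That makes the bias possible rather than demonstrated.
- **Adjustment.** Baseline adjustment removes much of a difference in stable fitness, so the raw 12.5 to 37.5 m overstates the harm from selective consent. Adjustment does not correct a shift in the baseline score that allocation itself caused.

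None of this answers the stated sequence: randomise, then measure an effort-dependent baseline, in a trial where pupils know their arm.

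**Conclusion.** The point holds in limited form. As the Design section is written, the baseline Cooper run is a post-allocation measure in an open trial, and it is later used for adjustment. It can therefore be influenced by allocation. Because consent is not said to precede allocation, the make-up of the consenting sample may be influenced too.

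The documents do not support the claim that the consenting samples have in fact lost the protection of randomisation, nor any particular size of bias. The 10 to 36 m range for a baseline shift rests wholly on assumed values of shift and slope. The direction is uncertain, and extra effort in intervention schools would hide part of a true effect. This is an inexpensive improvement to the order of events, not a demonstrated bias. It is best made before baseline, since the order cannot be restored once baseline has been collected.

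**What to change.** Change the Design section so that pupil consent, assent and baseline measures are completed in all seven schools, with the same assembly information, before allocation is made or disclosed and before any arm-specific briefing on the scheme. State in the Participant recruitment section where consent falls relative to randomisation.

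Where schools are already allocated, withhold the allocation from pupils until baseline is complete, if that is still possible. The article already gives the four-to-three split and describes peer nomination partly in the past tense, so full reversal may no longer be available. In either case, report consent rates and baseline Cooper results by arm so that readers can judge whether the groups differed at entry.

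The cost is less lead time between allocation and the voucher and peer-mentor set-up in intervention schools. No sample size or analysis model needs to change.

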## Participant recruitment

Following initial school recruitment, participants will be recruited for primary and secondary outcome measures via Year 9 assemblies. During the assemblies, researchers on the project (DC & MJ) will provide information about the project and answer any questions before distributing project information, parental consent and pupil assent forms after the assembly. Once consent and assent has been obtained, participants will be eligible to partake in the study.

## Intervention

The ACTIVE intervention consists of three different components; a) physical activity vouchers, b) peer mentor scheme, advocacy meetings and pupil-led video production, and c) support worker engagement.

### Physical activity vouchers

The intervention involves provision of vouchers equating to a monetary value of £20 (four vouchers in increments of £5) per pupil each month for 12 months. They are to be distributed in schools with the purpose of being used to; i) spend on existing activities, ii) fund new activities in the schools or communities such as fitness classes, and iii) purchase sporting equipment for themselves or a club. The vouchers are to be treated similar to a cash transaction but without the delivery of change, in order to prevent the purchase of non-PA based items. At the end of each month, vouchers will be collected from each provider with an accompanying invoice for reimbursement of fees. This transaction process has been informed by the ACTIVE feasibility study [7]. Activity providers (for example, leisure centres and sports clubs) have been recruited during the development stages of the project and will continue to be recruited throughout the intervention based on pupil suggestions.

### Peer mentoring scheme, advocacy meetings and pupil-led video production

Prior to baseline measures, pupils from each school will be asked to identify key influencers to be peer mentors (10 from each school). A peer nomination questionnaire was given to all pupils in the year and those who received the most nominations were invited to be peer supporters [31]. These individuals will receive training to be ‘peer supporters’ from the Active Young People team at Swansea Council and a student from the PR and Marketing Taught Masters course at Swansea University. The role of peer supporter is to encourage the uptake and sustainability of physical activity. This approach has been underpinned by ASSIST (A Stop Smoking in Schools Trial); an intervention which involved training Year 8 students to promote the benefits of not smoking amongst their peers. [32].

Peer mentors will be encouraged to produce videos throughout the intervention to explain why activity is important to them, the barriers to being active and any recommendations to improve activity for teenagers. These will help provide an innovative way to display the work of the ACTIVE intervention at advocacy meetings. These videos will be uploaded to YouTube and shown to local stakeholders and providers. Using an ACTIVE profile, videos will be recorded via ‘Snapchat’, a popular image-messaging app. Studies have shown that ‘Snapchat’ is used to facilitate relationships and ‘bonding’ amongst social circles [33, 34] and combined with its use of filters and text will create a novel way of displaying physical activity perceptions of this age group.

Throughout the ACTIVE intervention, advocacy meetings will be held with key stakeholders in order to promote sustainable investment for the provision of physical activities in the local community. These meetings will occur at 6 months and 12 months and involve discussion of needs, barriers to activity and changes that could improve teenager’s access and uptake from the peer mentors’ point of view.

